#### Strategies to improve adherence to interventions

Participants are supported by a physiotherapist to remove their sling as they feel able or to maintain the sling in place for 4 weeks, depending on their allocated intervention. Participants are also supported by a physiotherapist to adhere to their prescribed exercise programme through the individual consultations and a study specific manual and website that detail the exercises and progressions. Participants are also asked to complete a sling use diary to record their time out of the sling at regular periods throughout the day for 4 weeks postrandomisation.

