#### Secondary outcome measures

Shoulder pain and disability at 6 and 12 months postrandomisation will be measured using the total SPADI score.Health-related quality of life at 12 weeks, 6 and 12 months postrandomisation will be measured using the EQ-5D-5L.Time to return to usual activities, including work and driving, will be measured via self-report questionnaire at 12 weeks, 6 and 12 months.Healthcare resource use at 12 weeks, 6 and 12 months will be measured via self-report questionnaire.Rotator cuff repair integrity (evidence of full-thickness re-tear; yes/no) at 12 months will be assessed via diagnostic ultrasound scan.Number and nature of AEs at 12 weeks, 6 and 12 months will be measured via self-report questionnaire and clinician report.Self-report time out of the sling, measured in hours, over 4 weeks postsurgery via self-report diary.

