### Statistical methods

#### Primary and secondary outcome analysis

Primary analyses will be conducted according to the intention-to-treat analysis group. ANCOVA will be used to compare total SPADI scores between individualised EPDR versus standard rehabilitation at 12 weeks after randomisation, adjusting for baseline SPADI score.

Among other secondary analyses, time to return to usual activities (work and driving) will be analysed using Kaplan-Maier curves and log rank test. Logistic regression will be undertaken to test the association between treatment groups and re-tear at 12 months. Linear regression will be used to test the association between treatment groups and time out of the sling over 4 weeks. Repeated measures ANCOVA will be used to test if any treatment effect exists and has been maintained up to 12 months in terms of SPADI and EQ-5D-5L scores. ANCOVA will be used to compare total SPADI and EQ-5D-5L scores between the treatment groups at 6 and 12 months adjusting for baseline scores. Safety analysis will be undertaken based on the per-protocol analysis group. The presence of AEs/serious AEs and problems after surgery will be compared between the two groups at 12 weeks, 6 and 12 months using χ^2^ test.

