#### Definition of analysis population relating to protocol non-adherence and any statistical method to handle missing data

Per-protocol analysis will consider patients with time out of the sling of 222.6 hours or more over 4 weeks compared with those with time out of the sling less than 222.6 hours base on the cut-off values from the RaCeR pilot.^6^ Missing values in the diary will not be included in the analysis.

Complete-cases analysis will be undertaken as part of the primary endpoint analyses, where cases with missing values or those completed outside the 4 weeks window will be excluded in each analysis. If substantial missing data (>10% and <20%) are observed in SPADI at 12 weeks or a key prognostic covariate for the primary analysis, then multiple imputation using chained equations will be applied. Complete-cases analysis will be undertaken for the secondary study outcomes.

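### Adverse events are compared in a per-protocol group defined by hours out of the sling, so the harms comparison is not a randomised one

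*Protocol article*

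**What the plan says.** Under Primary and secondary outcome analysis, the primary analyses follow intention to treat, but "Safety analysis will be undertaken based on the per-protocol analysis group". The next sentence gives the comparison, by chi-square test: "The presence of AEs/serious AEs and problems after surgery will be compared between the two groups at 12 weeks, 6 and 12 months".

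The article's only definition of the per-protocol group is in the section on analysis populations and missing data: "Per-protocol analysis will consider patients with time out of the sling of 222.6 hours or more over 4 weeks". The comparison group is everyone below that threshold, which is taken from the pilot. Allocated arm is not mentioned. The same paragraph adds: "Missing values in the diary will not be included in the analysis".

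The hours come from a diary in which participants "record their time out of the sling at regular periods throughout the day for 4 weeks postrandomisation" (Strategies to improve adherence to interventions). They are also a secondary outcome: "Self-report time out of the sling, measured in hours, over 4 weeks postsurgery via self-report diary" (Secondary outcome measures). AEs are collected separately, by questionnaire and clinician report, up to 12 months. The article states no harms comparison by allocated arm.

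**The concern.** Time out of the sling is behaviour after randomisation, and the article itself ties it to symptoms. The description of individualised EPDR has sling removal progressing within the participant's pain and tolerance. AE reporting and harms lists increased shoulder pain needing additional care, and stiffness, among possible AEs. A participant allocated to EPDR who has an early painful complication may keep the sling on and fall below 222.6 hours because of it. That AE is then counted with the sling-wearers or left out of the comparison.

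The safety of early movement is a question the trial has to answer credibly. The Recruitment strategies section expects hesitation over its perceived risks, the trial is open-label, and no separate data monitoring committee is planned. A harms comparison in groups formed partly by the harms cannot give that assurance.

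**Working it through.** **The plan's own figure.** The only number on this point is the cut-off. 222.6 / 28 days = 7.95 h per day, and 222.6 / 672 h = 33% of the 4 weeks. It is attributed to the pilot and cannot be checked from the article.

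**Two readings of the definition.**
- *Split by hours:* everyone at or above 222.6 h against everyone below, whatever their allocation. AEs move between groups.
- *Arm and adherence:* EPDR participants at or above the cut-off against standard participants below it. Non-adherers and their AEs are dropped.

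Under either, participants without usable diary data may be lost.

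**Assumed inputs (none is in the article).** Equal arms. AE risk 22.5% EPDR and 15% standard, so the true risk ratio (RR) is 22.5 / 15 = 1.5. Hours out of the sling are normal: mean 300 (SD 120) in EPDR, mean 120 (SD 80) in standard. Diary unusable in 20% of participants without an AE and 30% with one. An early AE cuts hours by 0 or 60; a fraction *q* of AEs is early enough to do so.

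**Chance of reaching 222.6 h.**
- EPDR, no shift: Φ((300 − 222.6)/120) = Φ(0.645) = 0.741. Minus 60 h: Φ(0.145) = 0.558.
- Standard, no shift: 1 − Φ((222.6 − 120)/80) = 1 − Φ(1.2825) = 0.100. Minus 60 h: 1 − Φ(2.0325) = 0.021.

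With no shift, about 0.259 × 319 = 83 EPDR and 0.100 × 319 = 32 standard participants lie on the other side of the cut-off from most of their arm (before diary losses).

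**Share of each arm analysed.** With an AE: 0.225 × 0.7 = 0.1575 EPDR and 0.15 × 0.7 = 0.105 standard. Without: 0.775 × 0.8 = 0.62 and 0.85 × 0.8 = 0.68.

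**Split by hours, no shift.**
- At or above: AEs 0.1575 × 0.7405 + 0.105 × 0.0998 = 0.1271; no AE 0.62 × 0.7405 + 0.68 × 0.0998 = 0.5270. Risk 0.1271 / 0.6541 = 19.4%.
- Below: AEs 0.2625 − 0.1271 = 0.1354; no AE 1.30 − 0.5270 = 0.7730. Risk 0.1354 / 0.9084 = 14.9%.
- RR = 1.30.

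**Split by hours, 60 h shift, all AEs early.**
- At or above: AEs 0.1575 × 0.5576 + 0.105 × 0.0211 = 0.0900. Risk 0.0900 / 0.6170 = 14.6%.
- Below: AEs 0.1725. Risk 0.1725 / 0.9454 = 18.2%.
- RR = 0.80.

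For intermediate *q*, the chance of reaching the cut-off given an AE is (1 − *q*) × unshifted + *q* × shifted. For *q* = 0.5 in EPDR this is 0.649.

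| 60 h shift applies to | Split by hours: risks, RR | Arm and adherence: risks, RR |
|---|---|---|
| no AEs | 19.4% v 14.9%, 1.30 | 20.3% v 13.4%, 1.51 |
| a quarter | 18.3% v 15.8%, 1.16 | 19.2% v 13.6%, 1.41 |
| half | 17.1% v 16.6%, 1.03 | 18.2% v 13.9%, 1.31 |
| all | 14.6% v 18.2%, 0.80 | 16.1% v 14.4%, 1.12 |

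Analysing all participants by allocated arm returns 1.5 in every row.

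**No true difference (15% in both arms), same rows.** Split by hours: 1.00, 0.89, 0.79, 0.60. Arm and adherence: 1.00, 0.93, 0.86, 0.72.

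**Sensitivity.** With diary loss at 20% whether or not there was an AE, the split gives 1.30, 1.16, 1.03 and 0.80, and the arm-and-adherence set 1.50, 1.40, 1.30 and 1.11. The distortion comes from grouping by hours, not from the assumed diary loss.

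**The case against.** Several limits on this point stand.

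- **Re-tear is not affected.** A reader might infer that the key structural harm is compromised. It is not: re-tear at 12 months, assessed by ultrasound, is analysed by logistic regression on treatment group. The problem is confined to the AE, serious AE and post-surgery problem comparison, where re-rupture enters only if it needs additional care.
- **Timing limits the direct effect.** Hours cover 4 weeks, while AEs are compared to 12 months. Later events cannot change the hours; they can be affected only through confounding, for example by early pain or tear size. A reader might conclude that a true harm would reverse. In the table it does so only when every AE is early enough to cut hours by 60. With half or a quarter early, the effect is dilution.
- **The missing-diary sentence is ambiguous.** It may mean only that blank entries are not counted, so exclusion of participants is a possibility. The 30% diary loss among those with an AE is an input to the illustration, not a finding.
- **The direction is conditional.** Bias towards early mobilisation requires that AEs reduce time out of the sling. The article makes that plausible for pain but offers no data for infection or other events.
- **Harms by treatment received can be a legitimate supplement.** The article does not justify barring the 222.6 h grouping altogether.

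It might also be said that the full protocol or the analysis plan may add a safety analysis by arm. That does not answer the point, because the article does not leave the safety population open; it names one.

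**Conclusion.** The rule is wrong as written. The only stated basis for comparing AEs is a group defined by self-reported behaviour after randomisation, which the article's own account links to pain and hence to early harm. The comparison is unrandomised under either reading of the definition.

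The size cannot be known from the article. Under the stated assumptions a true RR of 1.5 appears as 0.80 to 1.30 when split by hours and as 1.12 to 1.51 when allocated arm is also required, depending on how many AEs are early enough to alter sling use. The arm-and-adherence reading does little damage if AEs do not affect sling use. The split by hours dilutes the effect even then. Loss of randomisation does not depend on these inputs; the amount and direction of bias do.

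**What to change.** Under Primary and secondary outcome analysis, replace the sentence that sets the safety population with: *Safety analyses will include all randomised participants, analysed in the group to which they were allocated, regardless of sling use or diary completion.*

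Any harms analysis by sling hours should be kept only as a supplementary, exploratory analysis and labelled as such. It should say whether allocated arm is part of the definition and how incomplete diaries are handled.

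The cost is one sentence in the protocol and the matching line in the analysis plan. AEs are already collected independently of the diary, so no new data are needed. The sample size of 638 and the rehabilitation schedules do not change.

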#### Interim analyses

Interim descriptive analysis will be undertaken at 6 months from the start of recruitment to assess the progression criteria of the internal pilot phase. This will not include any comparison of the patient reported outcomes between the randomised groups.

#### Methods for additional analyses

Exploratory subgroup analysis will be undertaken for the primary endpoint at 12 weeks including an interaction term in the ANCOVA model of ‘rotator cuff tear size’ by ‘treatment group’.

#### Definition of analysis population relating to protocol non-adherence and any statistical method to handle missing data

Per-protocol analysis will consider patients with time out of the sling of 222.6 hours or more over 4 weeks compared with those with time out of the sling less than 222.6 hours base on the cut-off values from the RaCeR pilot.^6^ Missing values in the diary will not be included in the analysis.

Complete-cases analysis will be undertaken as part of the primary endpoint analyses, where cases with missing values or those completed outside the 4 weeks window will be excluded in each analysis. If substantial missing data (>10% and <20%) are observed in SPADI at 12 weeks or a key prognostic covariate for the primary analysis, then multiple imputation using chained equations will be applied. Complete-cases analysis will be undertaken for the secondary study outcomes.

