### Interventions

#### Individualised EPDR

EPDR is an individualised approach where shoulder movement, sling removal and exercise are progressed as the participant feels able within the context of their own pain experience and tolerance. Individualised EPDR includes advice to the patient from a physiotherapist within 24 hours following surgery to remove their sling and gradually begin to actively use their arm as they feel able and within acceptable limits of pain. The advice to remove the sling is complemented by an exercise programme supervised by a physiotherapist and practised at home. After the first session with the physiotherapist, participants access follow-up with a physiotherapist according to usual care agreements. Follow-up sessions can be either face to face or remote.

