#### Standard (delayed) rehabilitation

Standard (delayed) rehabilitation includes advice to the patient from a physiotherapist within 24 hours following surgery to wear their sling for 4 weeks except for when eating, washing, dressing or undertaking the exercises prescribed. After the first session with the physiotherapist, participants access follow-up with a physiotherapist. The exercise programmes will be staged as follows^6^:

Stage 1: Fully assisted (passive) shoulder movement.

Stage 2: Partially assisted (active assisted) with progression to full non-assisted (active) shoulder movement.

Stage 3: Resisted static exercises (isometric).

Stage 4: Resisted exercises through shoulder range of movement (dynamic) within limits of pain progressing to functional restoration.

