#### Primary outcome measure

Shoulder pain and disability at 12 weeks postrandomisation will be measured using the SPADI. The SPADI is a validated self-report measure,^7^ it was more sensitive and responsive than the Oxford Shoulder Score in our RaCeR pilot and is the most used outcome measure in RCTs evaluating interventions for shoulder disorders.^6^

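### The per-protocol contrast is defined by observed sling hours rather than allocated arm, so as written it is an as-treated comparison open to confounding by early pain, and the safety analysis rests on it

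*Protocol article*

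**What the plan says.** The Protocol article, in the section defining the analysis population in relation to non-adherence, sets the rule: "Per-protocol analysis will consider patients with time out of the sling of 222.6 hours or more over 4 weeks". The other side of the comparison is everyone under the same figure, which is taken from the pilot. On incomplete diaries the section says: "Missing values in the diary will not be included in the analysis". No allocated arm and no adjustment is named.

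Four other places bear on this rule:

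- **Individualised EPDR:** "shoulder movement, sling removal and exercise are progressed as the participant feels able within the context of their own pain experience and tolerance".
- **Standard (delayed) rehabilitation:** the advice is "to wear their sling for 4 weeks except for when eating, washing, dressing or undertaking the exercises prescribed".
- **Secondary outcome measures:** sling time is itself an outcome observed after randomisation: "Self-report time out of the sling, measured in hours, over 4 weeks postsurgery via self-report diary".
- **Primary and secondary outcome analysis:** the primary analysis is intention to treat. The safety analysis is assigned to the per-protocol group, with adverse events compared between two groups by a χ² test.

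**The concern.** A per-protocol analysis normally keeps the randomised arms and removes participants who departed from their allocated treatment. Here the two sides are formed by hours out of the sling. Read literally, a standard-arm participant with many hours out joins the early-mobilised side, and an EPDR participant with few hours joins the other.

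This causes two problems in this trial. First, an EPDR participant who keeps the sling on because of pain is following that arm's instructions, so low hours are not in themselves non-adherence. Second, the trial's own definition of EPDR ties sling time to pain, and "Shoulder pain and disability at 12 weeks postrandomisation will be measured using the SPADI". Anyone whose early pain is mild can be expected to leave the sling sooner and, if early pain carries forward, to score better at 12 weeks whatever rehabilitation does.

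The documented use at stake is safety. The events listed under AE reporting and harms include increased shoulder pain needing further care and re-rupture needing further care. On the literal reading these would be compared between groups partly sorted by pain, and participants without usable diary data could drop out of the comparison.

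**Working it through.** **The plan's own figure.** The cut-off comes from the pilot and cannot be re-derived from this document. On its scale, 222.6 / 28 days = 7.95 hours a day, and 222.6 / (28 × 24 = 672) = 33% of the four weeks.

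**Inputs from the document (Sample size).** SD of SPADI 30; target difference 8; allocation 1:1. The only correlation given, 0.2, is between preoperative and 12-week SPADI. It says nothing about early postoperative pain.

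**Assumed inputs (not in the document).** Hours out of the sling: EPDR mean 300 (SD 120), standard mean 120 (SD 80), both normal. Correlation of early pain with hours −a, with a = 0.2 to 0.4. Correlation of early pain with 12-week SPADI b = 0.3 to 0.5. True treatment effect zero.

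**Step 1, position of the cut-off.** EPDR: (222.6 − 300)/120 = −0.645, so 74.05% lie above; normal density 0.324. Standard: (222.6 − 120)/80 = 1.2825, so 9.98% lie above; density 0.1753. The share placed opposite to allocation is (25.95% + 9.98%)/2 = 18%.

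**Step 2, formula.** Spurious difference = −30 × a × b × K, where K is the difference in mean standardised hours (the part linked to pain) between the two sides.

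- Split on hours, pain acting in both arms: K = (0.324 + 0.1753) × (1/0.8403 + 1/1.1597) = 1.025. Here 0.8403 = 0.7405 + 0.0998 and 1.1597 = 0.2595 + 0.9002.
- Split on hours, pain acting in EPDR only: K = 0.324 × (1/0.8403 + 1/1.1597) = 0.665.
- EPDR at or above the cut-off versus standard below it, pain in both arms: K = 0.324/0.7405 + 0.1753/0.9002 = 0.632.
- The same, pain in EPDR only: K = 0.324/0.7405 = 0.4375.
- By allocation, everyone included: K = 0, by randomisation.

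**Step 3, results (SPADI points, no true effect).**

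| a | b | 30ab | Split, both arms | Split, EPDR only | Arm-specific, both arms | Arm-specific, EPDR only |
|---|---|---|---|---|---|---|
| 0.2 | 0.3 | 1.8 | −1.8 | −1.2 | −1.1 | −0.8 |
| 0.2 | 0.5 | 3.0 | −3.1 | −2.0 | −1.9 | −1.3 |
| 0.4 | 0.3 | 3.6 | −3.7 | −2.4 | −2.3 | −1.6 |
| 0.4 | 0.5 | 6.0 | −6.1 | −4.0 | −3.8 | −2.6 |

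A simulation of 2,000,000 participants agrees to within 0.1 point in every cell, with about 0 by allocation.

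**Sensitivity.** If hours differ by 1 SD between arms, centred on the cut-off, K = 0.3521 × 2 × (1/1 + 1/1) = 1.408. With a and b both 0.2 the result is −30 × 0.04 × 1.408 = −1.7; with both 0.5 it is −30 × 0.25 × 1.408 = −10.6. The size depends heavily on the assumptions.

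**A true effect is also distorted.** Suppose allocation truly gave 8 points and pain played no part. EPDR participants make up 0.7405/0.8403 = 88.1% of the upper side and 0.2595/1.1597 = 22.4% of the lower side, so the split would show 8 × (0.881 − 0.224) = 5.3 points. The contrast is therefore not a clean estimate of the treatment effect even without confounding.

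**The case against.** The strongest reply is that the section concerns non-adherence, so the cut-off may be meant within arm: EPDR adherent at or above it, standard adherent below it. The safety sentence, which speaks of a per-protocol group and then of two groups, fits that reading. The full protocol or the analysis plan, not shown here, may say so. This stands as a possibility, but the article does not state it. It would also not cure the problem: the last two columns of the table still run from −0.8 to −3.8, and pain-limited EPDR participants would still be removed for following their instructions.

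It is also fair to say that the magnitudes are wholly assumed, and that the text supports pain-paced sling removal for EPDR only. That is why the EPDR-only columns are shown. They lower the upper end for the split from 6.1 to 4.0.

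A reader might infer more than the document supports:

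- **That the result would be reported as a treatment effect or used to rescue a null primary result.** Nothing gives the per-protocol analysis a confirmatory role. Intention to treat is primary, and the stated use of the per-protocol group is safety.
- **That participants with smaller tears leave the sling earlier.** The document offers no support for this.
- **That unrecorded diary time counts as zero, so that someone who discards the sling and stops recording scores low.** The more natural reading is exclusion of missing values, which brings selection rather than misclassification. The sentence does not settle which applies.

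**Conclusion.** The point holds as a fault in the rule as written. Observed sling time alone forms the comparison, which makes it as-treated under a per-protocol label, and the definition of EPDR supplies the confounder.

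With no true effect, the spurious benefit is about 1 to 6 SPADI points, or roughly 15% to 77% of the 8-point target (1.2/8 and 6.1/8). This rests on the assumed correlations and hours. The direction rests on pain-paced sling removal, which the document states, and on early pain persisting into the 12-week score, which is assumed.

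The primary analysis is not affected. The consequence falls on the per-protocol result and, more importantly, on the comparison of adverse events.

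**What to change.** Amend the definition before analysis:

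1. Do not use the 222.6-hour split to form comparison groups. Compare by randomised arm throughout.
2. If a per-protocol set is kept, exclude departures defined separately for each arm against that arm's own instructions. State that low hours in EPDR are not in themselves a departure, and that selection after randomisation remains.
3. Compare adverse events by allocated arm in all randomised participants.
4. Label any split on sling hours exploratory and non-randomised, and say how incomplete diaries are handled.

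An instrumental-variable or complier-average analysis with sling hours as the exposure should be exploratory at most. It needs allocation to act on SPADI only through sling time. The section on differences between care pathways says EPDR also changes exercise progression and resumption of activities, so that condition is doubtful. If those components produced the whole of an 8-point effect and sling time none, the analysis would credit all 8 points to sling hours.

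The cost is a small change of wording and one re-specified secondary analysis. No new data are needed.

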#### Implementation

The allocation sequence is generated by an online randomisation system. Following surgery, the local site team will explain to the participant their randomised allocation as well as other routine post-operative requirements. An exercise manual is provided to all participants, along with the sling diary. Participants will complete the diary with the amount of time (hours and minutes) they were not wearing the sling at regular periods throughout the day.

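### An absolute 222.6-hour sling cut-off is paired with a missing-entry rule that, read literally, counts each diary gap as sling wear, and that risks selection if incomplete diaries are excluded instead

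*Protocol article*

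**What the plan says.** All references are to the Protocol article.

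- Secondary outcome measures lists the variable: "Self-report time out of the sling, measured in hours, over 4 weeks postsurgery via self-report diary".
- Strategies to improve adherence to interventions asks participants to "record their time out of the sling at regular periods throughout the day for 4 weeks postrandomisation". Implementation confirms that an entry is the time "they were not wearing the sling at regular periods throughout the day". A larger entry therefore means less sling wear.
- Primary and secondary outcome analysis gives the model: "Linear regression will be used to test the association between treatment groups and time out of the sling over 4 weeks". The same section bases the safety analysis on the per-protocol group.
- The section on analysis populations and missing data defines the per-protocol comparison by "patients with time out of the sling of 222.6 hours or more over 4 weeks" against those below that figure, with the cut taken from the pilot. It then states "Missing values in the diary will not be included in the analysis". In its next paragraph it adds "Complete-cases analysis will be undertaken for the secondary study outcomes". The multiple imputation provided there covers 12-week SPADI and key prognostic covariates of the primary analysis, not the diary.

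**The concern.** The cut-off is a fixed number of hours, so it has its intended meaning only if the total covers all 28 days. The missing-entry rule lets the total cover fewer days and does not say how the total is then formed. Two readings are open. In the first, blank entries are left out and the recorded hours summed. In the second, a participant with an incomplete diary is left out altogether, as the complete-case sentence for secondary outcomes suggests.

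Under the first reading the error runs one way: less recording looks like more sling wear. Under the second, the result depends on who stops recording. Someone who no longer uses a sling has little reason to keep a sling diary, and one arm is advised to leave the sling off as they feel able. Missingness could plausibly depend on both arm and outcome.

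Sling time is the listed outcome that most directly shows whether the two arms were treated differently. Error in it blurs the measured separation and puts participants on the wrong side of the per-protocol cut. The adverse-event comparison inherits that misclassification.

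**Working it through.** **Inputs from the article:** cut-off 222.6 h; diary length 4 weeks = 28 days; entries record hours out of the sling. The cut-off itself comes from the pilot and cannot be re-derived here.

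**Step 1. The cut as a daily rate.** 222.6 / 28 = 7.95 h/day, or 222.6 / 672 = 33.1% of all hours.

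**Step 2. Missing days that move a participant below the cut if recorded hours are summed.** For a constant true rate h, find the largest number of recorded days d with h × d < 222.6; the missing days are 28 − d.

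| True h/day | True total (h) | Missing days | Summed total (h) |
|---|---|---|---|
| 8 | 224 | 1 | 27 × 8 = 216 |
| 9 | 252 | 4 | 24 × 9 = 216 |
| 10 | 280 | 6 | 22 × 10 = 220 |
| 12 | 336 | 10 | 18 × 12 = 216 |
| 16 | 448 | 15 | 13 × 16 = 208 |

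**Step 3. Recording stops early.** The rate needed to reach the cut is 222.6 / days recorded. After day 14 it is 15.9 h/day; after day 10, 22.3 h/day; after day 7, 31.8 h/day, which is impossible.

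**Step 4. The readings compared at group level (illustration only).** The article gives no sling-time distribution and no completion rate, so every input here is assumed: true means of 10 and 5 h/day, SD 4 between participants, a constant rate within participant, and incomplete diaries ending between day 10 and day 21. The last column is the early-arm share at or above 222.6 h.

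| Incomplete diaries (early / standard) | Handling | Arm difference (h) | Early-arm share |
|---|---|---|---|
| None (truth) | – | 134 | 70% |
| 20% / 20%, random | Summed | 122 | 59% |
| 20% / 20%, random | Excluded | 134 | 70% |
| 30% / 10%, random | Summed | 103 | 54% |
| 30% / 10%, random | Excluded | 134 | 70% |
| 30% / 10%, likelier with more time out | Summed | 97 | 51% |
| 30% / 10%, likelier with more time out | Excluded | 113 | 60% |

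Summing is biased in all three settings. Exclusion is biased only in the last.

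**Step 5. Does scaling to recorded days settle it?** Only if recorded days represent missing ones. Take an assumed participant out 5 h/day for 14 days who then leaves the sling for good and stops recording.

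- Summed: 14 × 5 = 70 h.
- Scaled: 70 × 28/14 = 140 h.
- True: 70 + 14 × 24 = 406 h.

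Summing and scaling both place this person below 222.6 h; the truth is above it.

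**The case against.** The strongest reply is that the article never says recorded hours are summed with gaps as zero. Sling time is a secondary outcome, and the complete-case sentence supports excluding incomplete diaries. On that reading no gap is taken as sling wear, and random missingness causes no bias. A third reading, hours per recorded time, would also leave missing values out and would largely remove the problem at a constant rate. Detailed diary scoring is often left to an analysis plan, which is not shown here. All of this stands, and it rules out some stronger statements:

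- A reader might infer that the plan definitely scores a gap as sling wear. That is the natural entry-level meaning of the sentence, but it is not stated.
- A reader might infer that every reading gives a wrong answer. Exclusion does not if missingness is random.
- A reader might infer that exclusion would leave almost nobody. With an assumed 4 entries a day (112 in all) and an independent 1% miss rate, 0.99^112 = 32% of diaries would be complete. But the article does not give the number of entries a day, and gaps from people who stop recording cluster in a few participants.
- A reader might infer that time out is bound to be understated. A blank may truly mean no time out, especially in the standard arm, and scaling would then overstate it.

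The reply does not remove the point. The article does not merely leave out a scoring rule; it states one. Beside an absolute-hours cut, that rule is biased on its literal reading. On the complete-case reading it discards usable diary days and is open to selection.

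**Conclusion.** The point holds as a stated rule that is poorly matched to the cut-off it serves. The threshold arithmetic needs only the article's own 222.6 h and 28 days: at a true 10 h/day, 6 missing days change the classification if entries are summed. The group-level figures in the working rest on assumed sling times and missingness. They show how the readings diverge, not how large the effect will be in this trial, which the article does not allow one to determine.

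Three analyses are affected: the regression of sling time on arm, the per-protocol split, and the safety analysis based on that split. A reader might infer that the main result is at risk. It is not: the primary comparison of 12-week SPADI is by intention to treat and does not use the diary, and neither does the sample size of 638.

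**What to change.** Replace the missing-diary sentence with a rule that does not count a gap as sling wear:

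1. Say whether missing means a blank period, a blank day or an unreturned diary.
2. For participants with at least a prespecified number of recorded days, take mean hours out per recorded day and scale to 28 days. For the rest, use multiple imputation, or fit a mixed model to the daily values.
3. Apply the 222.6 h cut to that total, after checking that this agrees with how the pilot scored its diary; otherwise the cut is not comparable.
4. Report diary completeness by arm.
5. Because scaling assumes that recorded days represent missing ones, add two sensitivity analyses: one counting time after recording stops as out of the sling, and one counting blank periods as zero hours out.

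The cost is a paragraph of wording and a little more analysis, with no new data. The main version carries a missing-at-random assumption, which the two sensitivity analyses are there to test.
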